### Treatment regimen

Three NKR-2 dose levels will be evaluated during this study, that is, 3×10^8^, 1×10^9^ and 3×10^9^ NKR-2 for each injection (adjusted to 4.6×10^6^, 1.5×10^7^ and 4.6×10^7^ NKR-2/kg, respectively, for patients with body weight below or equal to 65 kg) with a schedule of administration of three NKR-2 doses administered with a 2-week interval per patient. No systemic lymphodepleting preconditioning will be performed prior to NKR-2 injections.

### Trial endpoints

The *primary endpoint* of the *dose escalation* segment will be the occurrence of DLTs in all patients during the study treatment until 14 days after the last study treatment administration. *Secondary endpoints* will include the (i) occurrence of adverse events (AEs) and serious adverse events (SAEs) during the study treatment, (ii) occurrence of objective clinical response at D57, M3, M6, M9, M18 and M24 after first NKR-2 administration and according to international guidelines and (iii) progression-free survival (PFS) and overall survival (OS), and duration of response for patients with objective response up to 2 years after first NKR-2 administration.

The *primary endpoint* of the *expansion segment* will be the objective response rate (ORR) at D57, M3, M6, M9, M18 and M24 after first NKR-2 administration. *Secondary endpoints* will include the (i) PFS and OS, (ii) duration of response for patients with objective response up to 2 years after first NKR-2 administration and (iii) occurrence of AEs and SAEs and DLTs during the study treatment.

The overall aim of this segment is to understand the safety profile and develop initial observations of clinical activity in a cohort of up to 14 patients that support a deeper assessment of clinical efficacy of NKR2 in larger patient cohorts within a phase II clinical study.

Response to treatment will be assessed according to standard Response Evaluation Criteria In Solid Tumors (RECIST) criteria (version 1.1) for solid tumours or international recommendations for response criteria in haematological tumours. Apart from the visits scheduled per protocol, tumour assessment might also be performed at any time if considered as needed per investigator’s decision (eg, progression suspicion) and with regard to the RECIST 1.1. response confirmation.

### Study duration

For each patient, the overall study duration will be 15 years. The study consists of a screening phase, a treatment administration phase, a treatment follow-up phase and a long-term safety follow-up (figure 4). The duration of the administration phase will be 8 weeks, from Visit D1 to Visit D57. The duration of the treatment follow-up phase will be 22 months, from the end of the administration phase on D57 (Week 8) to Visit M24.

**Figure 4 F4:**
[figure not shown]
Overview of study phases. NKR-2 will be infused on days 1, 15 and 29. Tumour assessment will be done by tumour imaging and blood sampling for solid tumours and tumour imaging, blood, urine and bone marrow sampling for haematological tumours. BM, bone marrow; D, day; ICF, Informed Consent Form; M, month.

As per regulatory requirements, patients who received at least one NKR-2 treatment will need to be followed annually for a period of 15 years. Therefore, patients will also follow a *long-term safety follow-up* that will last for up to 15 years after the day of the first NKR-2 administration to collect safety data for 13 additional years. The surveillance will mimic as much as possible the standard follow-up of the respective tumour type, including monitoring of important safety parameters.

Patients may be withdrawn from the study treatment or from the study at any time at the patients’ discretion or at their investigator’s discretion. The investigator will document on the patient’s record whether the decision to discontinue treatment and/or study participation was made by the patient or the investigator and which reason applies.

In case of absence of disease progression at M24, PFS and OS as clinical endpoints will be followed up on a yearly basis or at ad hoc *basis*, that is, in case of progression/relapse suspicion. In case of disease progression at M24 or at any time before, the patient will be still asked to attend simplified follow-up procedures, which will include (i) record of survival status, (ii) medication status and (iii) blood sampling for viral copy number (VCN) and replication competent retrovirus (RCR) assessment. Clinical progression at the end of the treatment phase (D57) will not to be considered as a criterion for withdrawal from the study and will allow the continuation of the active follow-up of the patient with or without the initiation of a new anticancer therapy.

### Enrolment rules

There is no requirement for specific recruitment of each individual tumour indication to corresponding arm within the *dose escalation pha*se, but each dose level should enrol at least two different types of cancer. In each arm, patients will be enrolled at the next dose level when all evaluable patients at the same dose level have completed the safety period of 14 days after last NKR-2 injection. Within each dose level, patients will be enrolled as soon as the previous patient has received at least one NKR-2 administration and has completed the 14-day safety period after the first injection.

Enrolment in the *expansion segment* of the study will be performed in three steps, with a statistical analysis at the end of each step (see Adverse events, serious adverse events and dose-limiting toxicities section). Within each step, all patients can theoretically be enrolled at the same time.

Approximately 15 centres are expected to be initiated for patient enrolment in the expansion segment. Recruitment is anticipated to be completed within approximately 24 months. If this target is not met, then the recruitment period may be extended accordingly.

### Adverse events, serious adverse events and dose-limiting toxicities

All AEs starting from registration to 28 days after the last study treatment (Visit D57) must be recorded into the Adverse Event form in the patient’s electronic case report form (eCRF), irrespective of intensity or causality with study treatment.

To ensure patient safety, every SAE, regardless of suspected causality, occurring after the patient enrolment and until the administration phase concluding visit (at D57) must be reported to the sponsor within 24 hours of learning of its occurrence. Any SAEs experienced outside this period will only be reported to the sponsor if the investigator suspects a causal relationship to the study participation or if fatal SAEs occur after signature of the Informed Consent Form (ICF).

DLT refers to a toxicity that is experienced during treatment and within 14 days following any NKR-2 dose, is new and at least possibly related to study treatment. This includes any Grade 3 or higher toxicity or Grade 2 or higher autoimmune toxicity that cannot be controlled to Grade 1 or less within 72 hours with appropriate treatment, with the exception of Fever Grade 3 and immediate hypersensitivity reactions occurring within 2 hours of cell infusion that are reversible to a Grade 2 or less within 24 hours of cell administration with standard therapy.

Whenever a patient experiences toxicity that fulfils the criteria for a DLT, the study treatment will be interrupted. The standard time period for collecting and recording DLTs will be 14 days after each study treatment administration. AEs/SAEs that meet the definition of DLTs but that are reported outside of this time window will be reported as AEs/SAEs but not as DLTs.

The standard time period for collecting and recording pregnancy will begin at the first receipt of the product and last until the end of the study.

In addition to the above-mentioned reporting requirements and in order to fulfil international reporting obligations, SAEs that are related to study participation (eg, protocol-mandated procedures, invasive tests, a change from existing therapy) will be collected and recorded from the time the patient consents to participate in the study until she/he is discharged.

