### Toxicity management

As previously mentioned, the use of CAR T cells is limited by potentially severe toxicities, including CRS, neurotoxicity and tumour lysis syndrome (TLS), on-target off-tumour toxicity (related to recognition of the target antigen on normal tissues), clonality and insertional oncogenesis, vector persistence and immunogenicity. While these events may have been seen in relation with other CAR T cell therapies, and are provided for information, there are currently no events considered as expected for NKR-2 therapy (which can be different from other CAR T cell studies based on the unique mode of action) and all serious adverse reactions (SARs) will be considered as suspected unexpected SARs (SUSARs).

The management of toxicities related to CAR T cell therapies was described elsewhere^11 12 55^ but is evolving with everyday new information available from ongoing studies. Sites will be kept informed all along the study for any new therapeutic options modifications or standardisation between the different sites.

Briefly, CRS toxicity is currently of highest concern in the field. It is caused by a release of inflammatory cytokines such as interleukin (IL)-6, IL-2, Interferon (IFN)-γ and Tumour Necrosis Factor (TNF)-α, following the recognition of the target antigen, resulting in a systemic inflammatory response similar to sepsis. Therefore, CRS will correlate with both efficacy and toxicity in patients receiving T cell-engaging therapies. Tocilizumab (anti-IL-6) will be used as the first-line agent in the treatment of CRS. If the patient’s condition does not improve or stabilise within 24 hours of the tocilizumab dose, administration of a second dose of tocilizumab and/or a second immunosuppressive agent (such as corticosteroids) will be considered, based on the CRS revised grading system created by Lee *et al*^56^ to identifying severity and implementation of optimal care strategies for CRS.

TLS resulting in renal insufficiency, rapidly rising uric acid level or evidence of organ dysfunction will be managed with fluids and rasburicase as needed and as determined by the treating physicians.

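### After D57, whether a non-fatal new malignancy reaches the sponsor as an SAE depends on one investigator's causality judgement, for about 14.8 of the 15 scheduled years

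*Protocol article*

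**What the plan says.** All references are to the protocol article.

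The section *Adverse events, serious adverse events and dose-limiting toxicities* has two reporting regimes, divided at D57.

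- Up to D57: "All AEs starting from registration to 28 days after the last study treatment (Visit D57) must be recorded into the Adverse Event form", whatever their intensity or cause. Every SAE in the period goes to the sponsor within 24 hours, related or not.
- After D57: "Any SAEs experienced outside this period will only be reported to the sponsor if the investigator suspects a causal relationship to the study participation". Fatal SAEs are reported without that condition.

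The section's closing paragraph extends collection until the patient is discharged, but again for related events: "SAEs that are related to study participation (eg, protocol-mandated procedures, invasive tests, a change from existing therapy) will be collected and recorded". Pregnancy has its own rule: "collecting and recording pregnancy will begin at the first receipt of the product and last until the end of the study".

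*Toxicity management* lists, among potential toxicities of CAR T cells, "clonality and insertional oncogenesis, vector persistence and immunogenicity". It presents the list for information and says that no event is currently considered expected for NKR-2.

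*Study duration* sets follow-up of up to 15 years from the first administration, the last 13 of them for the collection of further safety data. On content it says: "The surveillance will mimic as much as possible the standard follow-up of the respective tumour type, including monitoring of important safety parameters". After progression a simplified follow-up applies, and its named items are survival status, medication status and blood sampling for viral copy number and replication competent retrovirus. Progression at D57 does not remove a patient; it "will allow the continuation of the active follow-up of the patient with or without the initiation of a new anticancer therapy".

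**The concern.** A new cancer is the clinical form that insertional oncogenesis would take, and it is one reason to follow recipients of a retrovirally modified cell product for many years. Under the stated rule, the sponsor receives a non-fatal case as an SAE only if the investigator at that site suspects a link to study participation.

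That judgement is hard to make from one case. All patients are relapsed or refractory, nearly all with prior anticancer therapy, and they may start a new anticancer therapy during follow-up, so another explanation is often at hand. The documents do not show how often it would be preferred. Each centre also sees few patients, so a pattern would more likely show in pooled cases than at one site. What is at stake is the completeness of the sponsor's SAE record for a late risk that the article itself names, and the chance for the sponsor and steering committee to judge cases together.

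**Working it through.** No sample-size or power formula applies. The check sets the stated rules side by side and then measures the scope of the conditional one.

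**Step 1. Which stated reporting rules would bring in a non-fatal new malignancy judged unrelated, after D57?**

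- AE recording irrespective of cause: ends at D57. No.
- SAE reporting irrespective of cause: ends at D57. No.
- SAE reporting after D57: needs suspected causality or a fatal outcome. No.
- Closing paragraph on SAEs until discharge: related events only. No.
- Handling of all serious adverse reactions as SUSARs (*Toxicity management*): a reaction already presupposes a suspected causal link. No.
- Event-triggered safety teleconferences (*Ethics and dissemination*): the triggers named are DLT, treatment-related SAE and SUSAR. DLTs are collected for 14 days after each dose, and the other two depend on relatedness. No.

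Every stated SAE route after D57 therefore passes through the causality judgement unless the event is fatal.

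**Step 2. How long does the conditional rule apply?**

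First, the article's own dates. The last dose is on D29, and 29 + 28 = 57, which agrees with D57. Total follow-up of 15 years less 24 months is 13 years, which agrees with the 13 additional years stated.

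- Scheduled follow-up: 15 × 365.25 = 5,479 days.
- Under the conditional rule: 5,479 − 57 = 5,422 days; 5,422 / 365.25 = 14.8 years.
- Under all-causality reporting, counted from first dose (D1 to D57): 56 days; 56 / 5,479 = about 1.0% of scheduled follow-up.

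**Step 3. To how many patients?**

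- Expansion: up to 86 (*THINK study design*).
- Escalation: at most 18 per arm in 2 arms, 2 × 18 = 36.
- Maximum treated: 86 + 36 = 122.
- Average per centre in the expansion segment, with about 15 centres (*Enrolment rules*): 86 / 15 = 5.7.

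**Step 4. What would asking about it cost?**

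- Contacts after D57: M3, M6, M9, M18 and M24 (5) plus 13 annual contacts in years 3 to 15 = 18.
- Entries at most: 122 × 18 = 2,196. If the annual schedule adds a year-1 contact, 122 × 19 = 2,318.

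The documents give no malignancy rate, so no expected number of cases can be computed.

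**The case against.** The strongest reply is that the rule governs what is reported as an SAE, not what is collected. *Study duration* states that the long-term phase exists to collect safety data and that surveillance covers important safety parameters. An article condenses the full protocol, and figure 4, which outlines the study phases, is not shown. Other routes exist as well: the sponsor's central database, regular safety data review meetings, and steering committee access to all safety data (*Ethics and dissemination*, *Patient confidentiality*). The remaining gap is also narrow. Fatal events are always reported, the threshold is any suspected link to study participation rather than to NKR-2 alone, and *Toxicity management* alerts investigators to insertional oncogenesis. Finally, limiting unrelated SAE reports after a defined window is a deliberate design choice.

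Much of this stands. A reader might infer that such a malignancy would go unrecorded because no follow-up item covers it. The documents do not support that: the simplified list is not shown to be closed, the safety parameters may include new malignancies, and the full protocol may name them. A reader might also infer that the article contradicts itself. It does not, since limited SAE reporting and continued scheduled data collection can coexist. Nor can anyone say from these documents that cases would be missed in any number.

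What the reply does not remove is the stated condition on sponsor SAE reporting. Databases and meetings can use only what reaches them. The section already makes one exception to the causality condition, for fatal SAEs, and gives pregnancy collection to the end of the study. Another exception would fit that structure.

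**Conclusion.** The point holds as a criticism of the stated causality filter. After D57, sponsor SAE reporting of a non-fatal new malignancy rests on one investigator's judgement for about 14.8 of the 15 scheduled years, for at most 122 patients. The sponsor should change this; confidence is medium.

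The conclusion rests on these assumptions:

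- A new malignancy counts as an SAE. The article does not define the term. If it did not count, the SAE rules would not reach it after D57 at all.
- Visits follow the nominal schedule. The 122 patients and 14.8 years are planned maxima, and mortality in a relapsed or refractory population will shorten actual follow-up.
- The figures describe the scope of the rule, not harm. No case count and no timing of insertional events is claimed.

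**What to change.** In the section on adverse events, serious adverse events and dose-limiting toxicities, add beside the exception for fatal SAEs: *Any new malignancy distinct from the enrolled tumour, from first NKR-2 administration to year 15, is reported to the sponsor whatever its suspected cause.* Progression of the enrolled tumour stays under the response rules.

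Ask about it (yes/no, type, date) at the follow-up contacts already scheduled, including the simplified follow-up if the item is not already there. Review reported cases at the planned safety data review meetings. If the full protocol already lists new malignancies, aligning the SAE rule with that list is enough.

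The cost is some additional reports, possibly unrelated to NKR-2, and one more question per existing contact: at most 2,196 entries (2,318 with a year-1 contact) if all 122 patients lived 15 years. No new visit, sample or meeting is needed.

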In the dose escalation segment, safety data will be monitored closely on an ongoing basis. The main analysis (leading to the selection of the RecD) will be conducted separately in each arm once all patients in the last dose level have received the three NKR-2 administrations and have completed the safety period (D43). All data related to the primary endpoints of the study will be analysed. The final analysis will be performed once all patients have attended the concluding visit of the follow-up phase (M24) or have been withdrawn from the study.

The expansion segment of the study will proceed in three steps, with a statistical analysis at the end of each step (figure 3). These steps aim to stop the study for futility in specific cohorts or specific tumour types in case of no (sufficient) responders in the corresponding cohorts at the time of analysis.

An interim analysis for futility will be performed on the first 14 patients over all 5 cohorts of patients with solid tumour types and on the first 6 patients over the 2 cohorts of patients with haematological tumour types who have either completed the administration phase (D57) or have withdrawn from the study.

The second step consists in cohort futility analyses after the first seven cancer patients in each tumour type have either completed the administration phase (D57) or have withdrawn from the study. At this step, an evaluation of the safety of the NKR-2 treatment in each cohort will also be performed on the first six patients who completed the 6-week treatment period (D43) or had a DLT. This will allow to adapt the RecD in any specific cohort (tumour type) according to both safety rules and futility analysis. Indeed, if, and as soon as, two or more DLTs have been reported within a specific cohort, and the criterion for futility was not reached, the next patients enrolled in this cohort will be treated at the next lower dose level. In contrast, if no DLT has been reported within a specific cohort, and the criterion for futility was not reached at Step 2, the next patients enrolled will be treated with the next higher dose level.

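### The DLT exclusion rule is keyed to when an event is reported, not when it starts; read literally, it can drop in-window toxicities from the count that sets the dose

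*Protocol article*

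**What the plan says.** The section *Adverse events, serious adverse events and dose-limiting toxicities* defines a DLT as a new, at least possibly related toxicity that is "experienced during treatment and within 14 days following any NKR-2 dose", with grade criteria added. It next sets a standard 14-day period after each administration for collecting and recording DLTs. It then adds that AEs and SAEs that "meet the definition of DLTs but that are reported outside of this time window will be reported as AEs/SAEs but not as DLTs".

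*Trial endpoints* makes the occurrence of DLTs, until 14 days after the last administration, the primary endpoint of dose escalation.

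The count is used in two places:

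- *THINK study design*: a 3+3 rule in each arm, with three patients added when one of three has a DLT. The recommended dose is the MTD or, if none is found, the highest dose evaluated.
- The expansion rules, printed under *Demographic characteristics*: provided futility is not reached, a cohort moves to the next lower dose once "two or more DLTs have been reported within a specific cohort", and to the next higher dose "if no DLT has been reported within a specific cohort".

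**The concern.** A DLT should be classified by when the toxicity begins relative to dosing. The date on which someone passes the information on says nothing about the drug. The exclusion sentence is worded by report date and is applied to events that already satisfy a definition based on onset. Anyone following it literally would reclassify a qualifying in-window toxicity as an ordinary AE or SAE because the report came late.

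The DLT count is the primary safety endpoint of escalation, fixes the recommended dose and moves the dose in the expansion cohorts. Late reporting can only take events out of that count, so any error goes towards a higher dose.

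**Working it through.** The protocol states no figure that depends on this sentence, so the check is of the text, followed by the consequence of one lost event.

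**1. What the sentence can act on.** Let D be the events that meet the definition. The definition includes the 14-day limit, so every event in D has its onset in a window.

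- If *reported* means reported, the sentence removes the events in D with a late report. All of these began in a window.
- If *reported* means occurring, the sentence removes the events in D with onset outside every window. There are none, so the sentence does nothing.
- It does sensible work only if *reported* means occurring and *definition* means the grade and relatedness criteria without the timing. That takes two silent corrections.

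**2. How the rest of the text expresses timing.** The same section sets the AE period by onset: "All AEs starting from registration to 28 days after the last study treatment". The escalation endpoint counts DLTs that occur, the 3+3 rule counts a patient who experiences one, and the cohort safety evaluation covers "the first six patients who completed the 6-week treatment period (D43) or had a DLT". The exclusion sentence is out of line with all of these.

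**3. Where a late report falls outside a window.** Infusions are on D1, D15 and D29 (Figure 4 legend, *Study duration*).

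- Dose 1: 1 + 14 = D15, the day of dose 2.
- Dose 2: 15 + 14 = D29, the day of dose 3.
- Dose 3: 29 + 14 = D43. No window follows.
- AE recording continues to 29 + 28 = D57, which is 57 − 43 = 14 days later.

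On schedule the windows adjoin, so a late report after dose 1 or 2 may fall in the next window. The exposure is therefore mainly after D43. It also arises when a dose is interrupted, as a DLT itself requires, or postponed, for which *Toxicity management* allows up to 4 weeks.

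**4. Effect of one lost DLT under the stated rules.**

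| Setting | True count | Action | Count after loss | Action |
|---|---|---|---|---|
| Escalation | 1/3 | add three patients | 0/3 | none added on account of a DLT |
| Expansion, futility not reached | 2/6 | next lower dose | 1/6 | neither rule triggered |
| Expansion, futility not reached | 1/6 | neither rule triggered | 0/6 | next higher dose, where one exists |

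One dose level is a factor of 1×10^9 / 3×10^8 = 3.3 or 3×10^9 / 1×10^9 = 3.0.

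**5. Frequency.** The document gives nothing on how often reports are late, so no probability is attached to these changes.

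**The case against.** The strongest reply is that this is one loose verb. Occurrence governs in the endpoint, in the 3+3 rule and in the DLT definition itself, and the sensible reading of the exclusion is *occurring outside the window*. That is very probably what was meant. It does not remove the point, because the sentence is itself a stated classification rule and gives a wrong count if followed as printed.

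The safeguards are also real. Under *Ethics and dissemination*, safety teleconferences take place at the end of each dose level and at any new DLT, treatment-related SAE or SUSAR, and all safety data are made available to an independent steering committee. *Toxicity management* treats every serious adverse reaction as a SUSAR. A misclassified event would be seen, but seeing it does not restore it to the formal count.

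A reader might infer more than the document supports:

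- *That the sponsor intends to discard late-reported DLTs.* The endpoint and the 3+3 rule point the other way.
- *That an ordinary compliant report would trigger the loss.* An SAE "must be reported to the sponsor within 24 hours of learning of its occurrence", so one learned of on D43 and sent on D44 would comply and still miss the window. This holds only if *reported* means notified to the sponsor. If it means recorded at the site, the event is inside.
- *That the expansion rules confirm a report-date rule,* because they speak of DLTs that have been reported. That is ordinary wording for a trigger that acts once events are known.
- *That the absence of a stated deadline for non-serious events, or the reach of the 72-hour clause, is part of the fault.* A condensed article may leave the first to the full protocol. The second is a separate question. An event that starts and is reported by D43 is not affected by the sentence, even if its outcome is known later.

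**Conclusion.** The concern holds as a wording error in a dose-setting rule, with minor severity. Read literally, the exclusion contradicts the onset-based definition and the occurrence-based endpoint, and it can remove qualifying in-window toxicities from the DLT count. Any such removal favours a higher dose. A single lost event can change the action taken at 1/3, 2/6 or 1/6, and the dose steps involved are 3-fold to 3.3-fold.

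The conclusion rests on the text as printed. It does not assume that late reports are common or that staff would apply the literal reading. The exposure is confined mainly to reports after D43 or around interrupted or postponed dosing. The document does not support a claim that the recommended dose will be too high.

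**What to change.** In the section on adverse events and DLTs, replace the phrase *reported outside of this time window* with *with onset outside of this time window*. Add one sentence: an event with onset in the window counts as a DLT whenever it is reported or confirmed. *Confirmed* is needed because part of the definition takes time to observe: it concerns toxicity that "cannot be controlled to Grade 1 or less within 72 hours with appropriate treatment".

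The 14-day window, the dosing schedule, the sample size and the decision thresholds stay as they are. The cost is a wording change, made through the written amendment procedure that the article already describes. The new wording does not by itself prevent a dose decision from being taken before a late report arrives. It ensures that the event is counted once it does.
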